### Secondary outcomes

5.2

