#### Inflammation indexes (from baseline to week 4)

5.2.2

We will monitor blood tests to certify if THJG could improve the inflammation condition, including the blood fat, *C*-reactive protein, tumor necrosis factor α, lymphocyte type, complement level, interleukin (IL, including IL-2, IL-6, IL-8, and IL-10), and immune globulin (Ig, including IgA, IgM, and IgG).

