### Statistical analysis

5.8

A trained statistician from CRC will complete all the statistical analysis, by Statistical Packages of Social Sciences software (version 24.0). Intention-to-treat approach for effectiveness and safety analysis will be used. As dealing the missing values, last-observation-carried-forward method will be applied. The mean ± standard deviation will be chosen for the description of continuous variables and the percentage is chosen to describe the variable values. Continuous variables, which are kept in the normal distribution, will be analyzed by Student *t* test; or else, nonparametric tests will be adopted. All statistical tests are 2-sided and *P* < 0.05 means statistically significant.

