## Discussion

6

The treatment of SCAD has been significantly improved in recent years, especially the inflammation theory gains more attention. But to benefit patients and ameliorate the inflammation condition as many, these treatments wait to be updated. THJG consists of *R corydalis*, *S persicae*, *F carthami*, *R chuanxiong*, *R paeoniae rubra*, *R salviae miltiorrhizae*, *R angelicae sinensis*, *R rehmanniae*, *Fructus aurantii immaturus*, *R cyperi*, and *Olibanum*. Previous study proved that the main components *S persicae* and *F carthami* could alleviate inflammation and regular apoptosis, suggesting the potential beneficial effect of THJG on SCAD that should be valued by critical-designed trial.

We went through PubMed, Web of Science, Embase, the Cochrane Library, China National Knowledge Infrastructure, Wan Fang Database, VIP Journal Integration Platform, Chinese BioMedical database, and Clinical Trials up to March 2019, noticing no evidence about the efficiency and safety of THJG in treating SCAD patients. Therefore, this clinical trial will be the 1st multicenter, randomized, double-blind, placebo-controlled research that investigates the efficacy, safety, and inflammation improvement of THJG in treating SCAD.

To assure the exploration reliability, we design a 3-center, randomized, double-blind, controlled clinical trial. In addition, TCM syndrome score, a widely used for evaluation of Chinese herbs treatment, will be used to measure the symptoms improvement of the SCAD patients. Inflammation indexs, SAQ, and MACE also will be observed. Furthermore, we will evaluate the patients’ quality of life using AIS and SF-36. The safety of THJG will be evaluated according to patients’ feelings and laboratory tests, such as blood routine, feces and urine routine, kidney and liver function, BNP, echocardiography, and electrocardiograph.

The outcomes of this research will answer whether THJG is an effective drug to treat SCAD, especially to improve the inflammation condition. Its positive results will offer SCAD patients and physicians a different treatment option. Furthermore, the trial can provide proof of THJG about life quality changing, drug safety, and symptom severity relieving.

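### The protocol promises an answer on inflammation from at least 12 secondary markers, each judged at P < 0.05, with no lead marker, direction or stricter criterion for that conclusion

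*Protocol article*

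**What the plan says.** **The rule.** Section 5.8 (Statistical analysis) states: "All statistical tests are 2-sided and" a P value below 0.05 is called significant. It draws no line between primary and secondary outcomes. Continuous variables are compared by t test or a nonparametric test.

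**The markers.** Section 5.2.2 gives their purpose: "We will monitor blood tests to certify if THJG could improve the inflammation condition". It names blood fat and C-reactive protein, then "tumor necrosis factor α, lymphocyte type, complement level, interleukin" ("including IL-2, IL-6, IL-8, and IL-10") and immunoglobulins ("including IgA, IgM, and IgG"). The comparison is from baseline to week 4. The section stands under the heading "Secondary outcomes". It names no lead marker, composite, order of testing or direction of improvement.

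**The conclusion.** Section 2.1 (Study design) names inflammation next to symptoms in the trial's purpose. The Discussion promises: "The outcomes of this research will answer whether THJG is an effective drug to treat SCAD, especially to improve the inflammation condition".

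**The concern.** The rule and the conclusion do not fit together. A 5% threshold per test controls the error of one comparison. The inflammation answer is to come from a set of a dozen or more comparisons, and the protocol does not say what pattern of results would justify it. With so many markers, a chance result on one or two is quite likely even if THJG has no effect, and nothing in the text prevents such a result from being reported as improved inflammation. The primary outcome, the TCM syndrome score at week 4, is not affected. At stake is the second question that the trial says it will settle.

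**Working it through.** The protocol states no error rate for the inflammation conclusion, so there is no figure of its own to reproduce.

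**1. Count the tests (section 5.2.2).** Blood fat, C-reactive protein, TNF-α, lymphocyte type and complement count once each: 5. Interleukins: 4. Immunoglobulins: 3. Total 5 + 4 + 3 = 12, with one baseline-to-week-4 comparison each. This is a minimum, because blood fat, lymphocyte type and complement are group terms that may each yield several results.

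**2. Inputs.** Two-sided α = 0.05 per test (section 5.8). No true effect on any marker. The correlation between markers is not in the document. I assume a common value and vary it.

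**3. At least one P < 0.05, either direction.** If independent: 1 − (1 − 0.05)^12 = 1 − 0.95^12 = 0.460. With correlation, from simulating 12 equally correlated normal test statistics (400,000 draws):

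| Correlation (assumed) | Either direction | Favourable direction only |
|---|---|---|
| 0 | 46.0% | 26.2% |
| 0.3 | 39.6% | 20.3% |
| 0.5 | 31.9% | 16.1% |
| 0.7 | 23.3% | 11.7% |

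**4. Favourable direction only.** This column applies if the direction of improvement were fixed in advance for every marker. Half of each test's 5% then counts: 1 − (1 − 0.025)^12 = 1 − 0.975^12 = 0.262 if independent.

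**5. Mixed case (assumption).** Suppose five markers have one obvious favourable direction, and the other seven (IL-2, IL-10, lymphocyte type, complement, IgA, IgM, IgG) could be read either way. If independent: 1 − 0.975^5 × 0.95^7 = 0.385. Simulation gives 33.5% at correlation 0.3 and 27.5% at 0.5.

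**6. Sensitivity to the count, either direction.** Without blood fat (11 markers): 1 − 0.95^11 = 0.431, and 30.3% at correlation 0.5. If the group terms expand to about 20 tests (assumption): 1 − 0.95^20 = 0.642, and 42.0% at correlation 0.5.

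**7. Power cost of an adjustment.** The strictest Holm step for 12 markers is 0.05/12 = 0.0042. With 40 per arm (section 5.7) and 80% power, the normal approximation to the detectable standardised difference is (z for α/2 + 0.842) × √(2/40):
- α = 0.05: (1.960 + 0.842) × 0.2236 = 0.63.
- α = 0.0042: (2.865 + 0.842) × 0.2236 = 0.83.

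The two-sample t calculation gives 0.63 and 0.85 SD.

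**The case against.** **The analysis plan may deal with this.** Multiplicity for secondary outcomes is often left to a statistical analysis plan, and only a protocol article is shown. The sentence in section 5.8 defines significance for one test and need not exclude a later adjustment. This stands as far as it goes, and the mere absence of an adjustment is not the point made here. The point rests on what the protocol does state: one threshold for all tests, together with a promised answer on inflammation. An analysis plan with an adjustment would still have to be reconciled with section 5.8, and the wording of section 5.2.2 and the Discussion would remain.

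**The markers are secondary.** There is one primary outcome, the sample size rests on it, and the promise is closing Discussion prose, not an analysis rule. Unadjusted secondary outcomes are acceptable when reported as supportive. That is why labelling the set exploratory is an adequate remedy. But sections 2.1 and 5.2.2 and the Discussion do not treat inflammation as merely supportive.

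**Two stronger readings are not supported.** A reader might infer that the protocol accepts any one significant marker as proof of improved inflammation. It does not say so. It is silent on whether one marker, several or the overall pattern would count. A reader might also take 46% to 32% as the chance of falsely claiming an improvement. Those figures count significance in either direction, and a rise in C-reactive protein, for example, could hardly be presented as a benefit. With all directions fixed in advance the range is 26% to 16%.

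Nor does the point need a tally of tests across all secondary outcomes. The text does not say that every questionnaire subscale is tested at every visit.

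**Conclusion.** The concern holds in limited form. The protocol promises an answer on inflammation, but its only criterion is P < 0.05 on each of at least 12 markers, and that does not hold the error of the answer at 5%.

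The size depends on an inferred rule (one significant marker taken as support) and on assumed correlations. For 12 markers it is 46% to 32% in either direction for correlations of 0 to 0.5, and 23% at 0.7. If only a prespecified favourable direction counts, it is about 26% to 16% for correlations of 0 to 0.5. Every case examined is above 5% by a clear margin.

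The correction should be made because it changes what the trial may conclude. It does not touch the primary analysis.

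**What to change.** 1. In section 5.2.2, list the individual components of blood fat, lymphocyte type and complement, so that the family of inflammation tests is defined.
2. In section 5.8, choose one of two rules. Either allow a conclusion that THJG improves inflammation only for markers significant after Holm adjustment across that family, or report the whole set as exploratory, with estimates and 95% confidence intervals.
3. Reword the Discussion sentence to match the choice.

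This costs a few sentences and no extra patients or data. With Holm there is a loss of power per marker: the effect detectable with 80% power rises from 0.63 to 0.85 SD at the strictest step for 12 markers, and further if the listed components make the family larger. The exploratory option avoids that loss but gives up the firm answer on inflammation.

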## Discussion

6

The treatment of SCAD has been significantly improved in recent years, especially the inflammation theory gains more attention. But to benefit patients and ameliorate the inflammation condition as many, these treatments wait to be updated. THJG consists of *R corydalis*, *S persicae*, *F carthami*, *R chuanxiong*, *R paeoniae rubra*, *R salviae miltiorrhizae*, *R angelicae sinensis*, *R rehmanniae*, *Fructus aurantii immaturus*, *R cyperi*, and *Olibanum*. Previous study proved that the main components *S persicae* and *F carthami* could alleviate inflammation and regular apoptosis, suggesting the potential beneficial effect of THJG on SCAD that should be valued by critical-designed trial.

We went through PubMed, Web of Science, Embase, the Cochrane Library, China National Knowledge Infrastructure, Wan Fang Database, VIP Journal Integration Platform, Chinese BioMedical database, and Clinical Trials up to March 2019, noticing no evidence about the efficiency and safety of THJG in treating SCAD patients. Therefore, this clinical trial will be the 1st multicenter, randomized, double-blind, placebo-controlled research that investigates the efficacy, safety, and inflammation improvement of THJG in treating SCAD.

To assure the exploration reliability, we design a 3-center, randomized, double-blind, controlled clinical trial. In addition, TCM syndrome score, a widely used for evaluation of Chinese herbs treatment, will be used to measure the symptoms improvement of the SCAD patients. Inflammation indexs, SAQ, and MACE also will be observed. Furthermore, we will evaluate the patients’ quality of life using AIS and SF-36. The safety of THJG will be evaluated according to patients’ feelings and laboratory tests, such as blood routine, feces and urine routine, kidney and liver function, BNP, echocardiography, and electrocardiograph.

The outcomes of this research will answer whether THJG is an effective drug to treat SCAD, especially to improve the inflammation condition. Its positive results will offer SCAD patients and physicians a different treatment option. Furthermore, the trial can provide proof of THJG about life quality changing, drug safety, and symptom severity relieving.

### Trial status

6.1

Recruitment will start in October 2019 and is expected to finish in January 2021.
